**TABLE C. Guidelines for Grading of Laboratory Abnormalities**

|  | **Grade 1**  **MILD** | **Grade 2**  **MODERATE** | **Grade 3**  **SEVERE** | **Grade 4**  **LIFE-THREATENING** |
| --- | --- | --- | --- | --- |
| **Hemoglobin**  ***(****g/dL)* | 9.5-10.5 g/dL | 8.0-94 g/dL | 6.5-7.9 g/Dl | < 6.5 g/dL |
| **Laboratory values** *(not otherwise specified)* | Abnormal but requiring no immediate intervention; follow | Sufficiently abnormal to require evaluation as to causality and perhaps mild therapeutic intervention | Sufficiently severe to require evaluation and treatment | Life-threatening severity; requires immediate evaluation, treatment, and usually hospitalization |

*Reference – WHO Toxicity Grading Scale for Determining the Severity of Adverse Events

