### 5.2. Selection criteria:

Patients shall be assessed for the inclusion criteria at the time they are referred to the study clinic with a screening thick blood smear parasitaemia of > 2000/ul and < 200,000/ul. If the following criteria are met, patients will be enrolled in the study, assigned a study number, have blood removed by finger-prick for further laboratory tests (Giemsa-stained thick and thin blood smears, Hb measurement and blood collected on filter paper) and will be treated promptly according to their assigned antimalarial study regimen.

1. Age 6 months and above.
2. Fever (> 37.5ºC axillary) or history of fever in the previous 24 hours.
3. Absence of any history of serious side effects to study medications, including allergy to sulphonamide drugs
4. No evidence of a concomitant febrile illness which could interfere with the assessment of clinical treatment outcome
5. Provision of informed consent and ability to participate in 28-day follow-up (patient has easy access to health unit).
6. No history of treatment with an antifolate (sulfadoxine-pyrimethamine [single dose], metakelfin [single dose], TMP/Sulfa [> 3 days]) or amodiaquine (> 2 doses) during the last week (taking final dose within the 7 days prior to study enrolment).
7. Absence of pregnancy (menstruating women who have not missed their last menstrual period).
8. No danger signs or evidence of severe malaria defined as:

- Unarousable coma (if after convulsion, > 30 min)
- Repeated convulsions (> 2 within 24 h)
- Recent convulsions (1-2 within 24 h)
- Altered consciousness (confusion, delirium, psychosis, coma)
- Lethargy
- Unable to drink or breast feed
- Vomiting everything
- Unable to stand/sit due to weakness
- Severe anemia (Hb < 5.0 g/dL)
- Respiratory distress (laboured breathing at rest)
- Jaundice (yellow coloring of eyes)

Prior to the Day 1 return visit, the study laboratory technicians shall assess the results of the Giemsa-stained thick and thin blood smears. These shall not be available until after the patients have been treated and discharged from the clinic. Additional patients will be excluded from the study on Day 1 if they fail to meet the following additional inclusion criteria.

1. *P. falciparum* mono-infection
2. Parasite density > 2000/ul and < 200,000/ul.

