### 7.2.2. Identification of adverse events:

At each follow-up visit (days 1, 2, 3, 7, 14, 21, 28, and any unscheduled day), study clinicians will assess patients according to a standardized clinical record form (Appendix 14). All signs and symptoms present will be graded as mild, moderate, severe, or life threatening according to examination guidelines (Appendix 6). An AE will be defined as a sign or symptom of untoward medical occurrence arising or increasing in severity compared to the previous day’s record.

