### APPENDIX 10. Adverse Event Reporting Guidelines

On Day 0 perform a careful history and physical exam and record your findings on the case record form (CRF), grading the patient reported symptoms and exam findings according to the guidelines presented in Appendices 3 and 4. Record the hemoglobin value and grade (Appendix 5) on the CRF as soon as they are available. All Day 0 values will serve as the patient’s baseline.

On all follow-up days, assess and grade the patient-reported symptoms and physical exam signs according to the guidelines in Appendices 3 and 4. Record the follow-up hemoglobin results obtained on Day 28 (and any extra day) and grade according to the guidelines in Appendix 5.

At each follow-up visit, evaluate the CFR for any reportable adverse events. Review for symptoms, physical exam signs, and hemoglobin results that are > grade 2 and are new or worsening by comparing the grade assigned on the follow-up day to the previous day’s record.

If a new or worsening symptom, sign, or laboratory value is present (increasing grade compared to the previous day’s value and > grade 2), answer “YES” in the appropriate column for reporting adverse events on the CRF (otherwise, answer “NO”).

An adverse event is defined as any “untoward” (unfavorable or undesirable) medical occurrence in a patient who has received a medication that may or may not be related to this treatment. Any event (patient-reported symptom, physical exam finding, or laboratory value) that occurs after treatment with a study medication that is new or worsening from Day 0 should be considered a possible adverse event, regardless of whether you think that the treatment caused the event.

The following scenarios are examples of adverse events (AEs):

|  | **Day 0** | **Day 1** | **Day 2** |
| --- | --- | --- | --- |
| Nausea | 0 | 0 | 2 |

AE = nausea on Day 2

|  | **Day 0** | **Day 1** | **Day 2** | **Day 3** |
| --- | --- | --- | --- | --- |
| Nausea | 2 | 1 | 0 | 2 |

AE = nausea on Day 3

For each new / worsening event of > grade 2, the following information will be collected on the Adverse Event Record Form:

1. Description of event
2. Date of event onset
3. Date event reported
4. Maximum severity of the event
5. Maximum suspected relationship of the event to study medication
6. Is the event serious?
7. Initials of the person reporting the event
8. Was the event episodic or intermittent in nature?
9. Outcome
10. Date event resolved

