###### APPENDIX 12. Expected Adverse Events for study medications.

| **Skin** | Skin rash  Pruritis  Depigmentation  Hair loss  Bluish-gray pigmentation of the fingernails, skin, hard palate  Erythema multiforme  Steven’s-Johnson Lyell’s syndrome |
| --- | --- |
| **GI** | Nausea  Vomiting  Diarrhea  Hepatitis  Feeling of fullness  Stomatitis |
| **Heme** | Leukopenia  Agranulocytosis  Aplastic anemia  Hemolytic anemia  Megaloblastic anemia  Thrombocytopenia  Purpura |
| **Eye** | Visual disturbances  Corneal deposits or opacities Retinal degeneration |
| **Neuro** | Peripheral neuropathy  Polyneuritis  Neurological and psychiatric changes  Convulsions  Psychosis |
| **Other** | Fever  Lethargy / fatigue  Headache  Allergic reactions  EKG changes  Cardiomyopathy  Pulmonary infiltrates |

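### The haemoglobin adverse-event rules contradict each other: the Appendix 10 grade-increase rule cannot register a fall within Grade 4, while the record-form footnotes count unchanged or improved values

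*Protocol*

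**What the plan says.** - **Grades.** Appendix 6, Table C, gives the last two haemoglobin cells, Grade 3 and Grade 4 (life-threatening), as "6.5-7.9 g/Dl | < 6.5 g/dL".
- **Entry limit.** Section 5.2 lists "Severe anemia (Hb < 5.0 g/dL") among the danger signs and severe-malaria criteria that bar enrolment. Appendix 13 repeats the limit.
- **Baseline.** Appendix 10: "All Day 0 values will serve as the patient’s baseline".
- **Grade-increase rule.** For a new or worsening symptom, sign or laboratory value, Appendix 10 has the clinician answer yes if there is "increasing grade compared to the previous day’s value and > grade 2", and no otherwise.
- **General definition.** Later in Appendix 10, any symptom, finding or laboratory value "that is new or worsening from Day 0 should be considered a possible adverse event". No grade step is named.
- **Section 7.2.2.** An adverse event is a sign or symptom "arising or increasing in severity compared to the previous day’s record". Laboratory values are not mentioned.
- **Record-form footnotes.** In Appendix 15, the laboratory page of both the two-arm and the three-arm form says that a haemoglobin measured after Day 0 is reported as an adverse event when its grade is above 2. Unlike the symptom and examination footnotes on the same forms, this one has no new-or-worsening condition.
- **Timing.** Section 7.1 repeats haemoglobin on Day 28 or at clinical treatment failure, so the preceding record is normally Day 0.
- **Use.** Section 4.2.2 compares the proportion of patients with adverse events, by severity and by specific sign or symptom, between the groups.

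**The concern.** One laboratory measurement is governed by three statements that do not agree. One requires a higher grade, one requires any worsening from Day 0, and one requires only a sufficiently bad later value. A clinician completing the form has both the Appendix 10 instruction and the footnote to follow, and nothing says which prevails.

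The disagreement matters most for patients who enter at 5.0-6.4 g/dL. They have no higher grade to move to, so the grade-increase rule is silent however far haemoglobin falls, including past the protocol's own severe-anaemia limit. Appendix 12 lists "Hemolytic anemia" among the expected events for the study medications, so a drug-related fall is foreseeable. In the same patients the footnote counts stable or recovering values as adverse events. Haemoglobin event counts could then differ between sites, or between the form and the analysis, for reasons unrelated to treatment.

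**Working it through.** **Inputs.** Table C grades: Grade 4 below 6.5; Grade 3 6.5-7.9; Grade 2 8.0 to just under 9.5 (its printed upper limit, 94, is read as 9.4 because Grade 1 starts at 9.5); Grade 1 9.5-10.5 g/dL. Entry is possible from 5.0 g/dL upward (Section 5.2). The comparator is Day 0 (Section 7.1).

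**Rules applied.** With G0 and G1 the Day 0 and follow-up grades, and H0 and H1 the values in g/dL:

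- A, Appendix 10 instruction: G1 > G0 and G1 above 2.
- B, record-form footnote: G1 above 2.
- C, Appendix 10 general definition: H1 < H0.

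| Day 0 to follow-up (g/dL) | Grades | A | B | C |
|---|---|---|---|---|
| 5.0 to 4.9 | 4 to 4 | no | yes | yes |
| 6.4 to 4.9 | 4 to 4 | no | yes | yes |
| 6.4 to 4.0 | 4 to 4 | no | yes | yes |
| 6.5 to 4.9 | 3 to 4 | yes | yes | yes |
| 9.0 to 4.9 | 2 to 4 | yes | yes | yes |
| 6.0 to 6.0 | 4 to 4 | no | yes | no |
| 5.5 to 6.2 | 4 to 4 | no | yes | no |

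These answers are the same whether the threshold is read as above Grade 2 or as Grade 2 and above.

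The first three rows show what rule A misses: a fall below 5.0 g/dL in a patient who entered above it. The last two show what rule B adds: an unchanged and an improved value. Rule B's over-count is not confined to Grade 4. A patient at 7.0 g/dL on both days is Grade 3 twice, again no under A and yes under B.

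**How many patients could be affected.** The documents give no haemoglobin distribution. Assume a normal distribution with mean m and SD 2 g/dL. The share entering at 5.0-6.4 g/dL is Φ((6.5 − m)/2) − Φ((5.0 − m)/2):

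- m = 11: Φ(−2.25) − Φ(−3.00) = 0.0122 − 0.0013 = 0.011, and 0.011 × 180 ≈ 2 per arm.
- m = 10: Φ(−1.75) − Φ(−2.50) = 0.0401 − 0.0062 = 0.034, and 0.034 × 180 ≈ 6 per arm.
- m = 9: Φ(−1.25) − Φ(−2.00) = 0.1056 − 0.0228 = 0.083, and 0.083 × 180 ≈ 15 per arm.

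The 180 is the adjusted group size in Section 8.1. These are patients for whom rule A cannot fire. They are not a count of patients whose haemoglobin then falls, which cannot be estimated from the documents.

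**The case against.** A reader might infer that a later fall into severe anaemia is not an adverse event in this trial. The documents do not support that. The footnote on both forms is specific to haemoglobin and would report it. The general definition in Appendix 10 makes it a possible event. Appendix 10 also classes laboratory abnormalities leading to a diagnosis of severe malaria as serious adverse events when parenteral quinine is required, and Appendix 13 lists haemoglobin below 5.0 g/dL as severe malaria. That last route depends on the diagnosis and the treatment, so it does not cover every fall. Only the grade-increase instruction fails to register it.

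Three other strong readings also fail:

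- The 6.5 and 5.0 g/dL limits do not contradict each other. One belongs to a toxicity scale, the other to a severe-malaria definition, and any four-grade scale has a ceiling.
- A Grade 4 label does not leave seriousness undefined. Appendix 10 says that seriousness rests on outcome or action taken and is not directly tied to severity.
- The Grade 2 cell, printed as 8.0-94 g/dL, is an evident lost decimal point.

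It is also fair to say that the forms record haemoglobin in g/dL at Day 0 and follow-up, so worsening can be recovered at analysis. Section 4.2.2 compares the change in mean haemoglobin from Day 0 to Day 28 directly, and that comparison does not use grades. Outcome assessors are blinded (Section 4.4), so the rule conflict gives no evident reason for bias towards one arm.

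All of this limits the consequence. It does not remove the conflict: for the same pair of values the protocol's own rules return opposite answers, and no text ranks them.

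**Conclusion.** The point holds as an inconsistency between the haemoglobin adverse-event rules, and it is minor. The grade-increase rule misses worsening within Grade 4; the record-form footnote counts values that are unchanged or better. The haemoglobin contribution to adverse-event incidence therefore depends on which page is followed.

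That conclusion rests on the text and the rule-by-rule table alone. The share entering at 5.0-6.4 g/dL, about 1% to 8%, rests on an assumed normal distribution with SD 2 g/dL and mean 9 to 11 g/dL. It bounds the group in which a grade increase is impossible, not the number of missed events. The primary efficacy comparison is not affected.

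**What to change.** Reconcile the Appendix 10 instruction, the Appendix 10 general definition and the haemoglobin footnotes on both record forms into one rule for the adverse-event analysis. It should:

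1. require worsening from Day 0, so that unchanged or improved values are not counted;
2. be able to register worsening within Grade 4 from the recorded g/dL values, with the fall that counts fixed by the investigators before the data are analysed;
3. appear in the same words in Appendix 10 and in both footnotes.

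Correct the upper limit of the Grade 2 cell in Table C as a clerical matter. No clinical cut-off is proposed here.

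The cost is a few sentences in Appendix 10, two footnotes and one table cell. No new measurement or visit is needed. If forms have already been completed, the rule can be applied to the recorded values at analysis.

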**Appendix 8: Patient Screening Form**

**STUDY SITE CODE:________ STUDY NUMBER: ___________________________**

UMSP SCREENING FORM

| **1. Names:** | **3. Date: *(dd/mm/yy)*** |
| --- | --- |
| **3. Age*: _______years __________months.** | **Gender: ______M _______F** |

**** Include months only if age < 5 years, if age is above 5 years write*** *“X”.*

| **SCREENING selection criteria**  ***Onlyscreen patients who are 6 months or older and have a positive screening thick blood smear*** | | |
| --- | --- | --- |
| **inclusion criteria** | **yes** | **NO** |
| 5. Fever (> 37.5C) or history of fever in previous 24 h |  |  |
| 6. Ability to participate in 28 day follow up. |  |  |
| **EXCLUSION CRITERIA** | **NO** | **YES** |
| 7. History of serious side effects to study medications  (Including sulfa allergy)  *If present, indicate drug / side effect:*   Amodiaquine:________________________   Artesunate (3-arm study only):_________________   Chloroquine:_________________________   SP:_________________________________ |  |  |
| 8. Evidence of severe malaria / danger signs  *If “ YES” indicate criteria. If “NO”, leave blank.*   Unarousable coma *(if after convulsion, > 30 min)*   Repeated convulsions *(> 2 within 24 h)*   Recent convulsions *(1-2 within 24 h)*   Altered consciousness  *(confusion, delerium, psychosis, coma)*   Lethargy   Unable to drink or breast feed   Vomiting everything   Unable to stand/sit due to weakness   Severe anemia *(Hb < 5.0 g/dL)*   Respiratory distress *(laboured breathing at rest)*   Jaundice *(yellow coloring of eyes)* |  |  |
| 9. Evidence of concomitant febrile illness  *If “YES”, indicate illness. If “NO”, leave blank.*   Pneumonia/RTI  Measles   Otitis Media  Other:___________________   Gastroenteritis |  |  |
| 10. Presence of pregnancy by LNMP  N/A |  |  |
| 11. History of Anti-folate or Amodiaquine use in past week  *If “YES”, indicate drug / date taken. If “NO”, leave blank.*   AQ (> 2 days):__________  Septrin (> 3 days):_______________  SP (single dose):_ _______  Metakelfin (single dose):__________ |  |  |
| **INCLUSION CRITERIA.** | **YES** | **NO** |
| 11. Provision of informed consent. |  |  |
| ***Complete prior to day 1 clinic visit.*** | | |
| 12. *P. falciparum* infection |  |  |
| 13. Parasite density > 2000/ul and < 200,000/ul |  |  |

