APPENDIX 16. UMSP ADVERSE EVENT RECORD FORM..…………………………………………..59

**1.0. Summary**

| **Title** | Combination therapies for treatment of uncomplicated malaria in Uganda: evaluation of efficacy, safety, and tolerability |
| --- | --- |
| **Description** | Randomised, single-blinded trials comparing combination antimalarial regimens for treatment of uncomplicated falciparum malaria with 28-day follow-up. |
| **Participants** | Ugandans age > 6 months. |
| **Clinical Sites** | The studies will be conducted at the seven Uganda Malaria Surveillance Project (UMSP) sentinel sites. The Ugandan Ministry of Health (MoH) originally established these sites in 1998 in collaboration with the East African Network for Monitoring Antimalarial Treatment (EANMAT). |
| **Selection Criteria** | 1. Age > 6 months. 2. Fever (> 37.5ºC axillary) or history of fever in the previous 24 hours. 3. Absence of any history of serious side effects to study medications, including allergy to sulfa drugs 4. No evidence of severe malaria or danger signs 5. No evidence of a concomitant febrile illness 6. *P. falciparum* mono-infection 7. Parasite density > 2000/ul and < 200,000/ul 8. Agreement to return for all scheduled follow-up visits 9. Provision of informed consent 10. No history of anti-folate or amodiaquine use in past 7 days 11. Absence of pregnancy |
| **Follow-up** | Subjects will be asked to return on Days 1, 2, 3, 7, 14, 21, 28, and any unscheduled day that they feel ill for follow-up assessment. |
| **Study objectives** | To assess the efficacy, safety and tolerability of alternative antimalarial therapies for treatment of uncomplicated falciparum malaria as they compare to chloroquine/sulfadoxine-pyrimethamine (CQ/SP) treatment. |

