### FOLLOW-UP EVALUATION AND PROCEDURES

7.1. Follow-up schedule:

Patients will go home on Day 0 and will be asked to return to the clinic for follow-up on Days 1, 2, 3, 7, 14, 21, 28, and any unscheduled day that they feel ill. All patients will be reimbursed the cost of their transport to and from the clinic. Details about the location of the patient’s residence will be obtained and if a subject does not return for a scheduled clinic follow-up appointment, the study personnel shall visit them at home. Patients who return on Day 1 and fail to fulfil the criteria of *P. falciparum* mono-infection with a parasite density of > 2000 parasites/ul and < 200,000 parasites/ul will be excluded from further study and referred to OPD for management. At each repeat visit, temperature will be measured and a focused physical examination will be performed. A finger prick blood sample will be obtained on Days 2, 3, 7,14, 21 and 28 (and any extra day) to repeat thick blood smears and to save on filter paper. Haemoglobin will be re-evaluated either on day 28 or at the time of clinical treatment failure. All thick smears will be assessed for parasite density and presence of gametocytes. Any patient who is suspected of clinical treatment failure after Day 3 will have a repeat thick and thin smear obtained.

Follow-up Schedule

|  | **Day 0** | **Day 1** | **Day 2** | **Day 3** | **Day 7** | **Day 14** | **Day 21** | **Day 28** | **Extra Day** | **When necessary** |
| --- | --- | --- | --- | --- | --- | --- | --- | --- | --- | --- |
| Study medications | X | X | X |  |  |  |  |  |  |  |
| History | X | X | X | X | X | X | X | X | X |  |
| Temperature measurement | X | X | X | X | X | X | X | X | X |  |
| Physical exam | X | X | X | X | X | X | X | X | X |  |
| Neurologic exam (3-arm study only) | X |  |  |  | X | X | X | X | * |  |
| Thick blood smear | X |  | X | X | X | X | X | X | X |  |
| Thin blood smear | X |  |  |  |  |  |  |  |  | CTF after day 3 |
| Filter paper sample | X |  |  | X | X | X | X | X | * |  |
| Haemoglobin | X |  |  |  |  |  |  | X | * | If CTF, on day of failure |
| Assessment for adverse drug event | X | X | X | X | X | X | X | X | X |  |

X = perform this task

* As indicated

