***If any of the responses fall into the shaded area, exclude the patient from the study***

**APPENDIX 9. UMSP ENROLLMENT FORM.**

| **enrollment form** | | |
| --- | --- | --- |
| **1. Study**  **Number:** | **2. Treatment**  **Number:** | **3. Start Date:**  ***(dd/mm/yy)*** |

| 4.Patients name: |
| --- |
| 5. Father’s name: |
| 6. Mother’s name: |
| 7. Primary caregiver / guardian’s name and relationship (N/A if mother or father): |
| 8. Sub county of residence. |
| 9. Home parish: |
| 10. LC1/village: |
| 11. Home address and localising features: |
| 12. a) Phone number: Yes ___No ___  If yes: b) Phone number (s) and the owner(s): |
| Patient Information |
| 13. Anti-folate use in the last 4 weeks? Yes ______ No________Unknown__________ |
| 14. Does the patient use malaria preventive measures: Yes ___No ___Unknown ____  If yes, which measures are used?    a) Spray: Yes ___No ___  b) Coils: Yes ___No ___  c) Chemoprophylaxis: Yes ___No ___  If yes, which drug? ___________________________________  e) Bed net: Yes ___No ____  If yes, is the net treated? Yes ___No ___   How often does the patient sleep under the net?  Always____ Often / Sometimes____  h) Other protective measures ______________________________________________________________ |

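### Screening-form item 12 (Appendix 8) omits the mono-infection requirement, so a mixed infection can pass the Day 1 eligibility check

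*Protocol*

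**What the plan says.** The Summary (Section 1.0) lists "6. *P. falciparum* mono-infection" among the selection criteria. Section 5.2 splits eligibility into two steps. Most criteria are checked on Day 0, but species and the confirmed parasite density come from the Giemsa-stained smears read before the Day 1 visit. It then says "Additional patients will be excluded from the study on Day 1 if they fail to meet the following additional inclusion criteria", and the first of these is "1. *P. falciparum* mono-infection". Section 7.1 repeats the rule: "Patients who return on Day 1 and fail to fulfil the criteria of *P. falciparum* mono-infection" or the density limits "will be excluded from further study and referred to OPD for management". The Day 1 box of the Appendix 1 flow chart has the same two criteria.

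The Patient Screening Form (Appendix 8) closes with two items under the instruction "Complete prior to day 1 clinic visit". The first is "12. *P. falciparum* infection" and the second is the density range. The form's exclusion rule follows: "If any of the responses fall into the shaded area, exclude the patient from the study".

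Section 8.2 limits the primary analysis to randomised patients who meet the selection criteria.

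**The concern.** Four places in the protocol require a single-species infection, and the form that puts the requirement into practice asks only whether *P. falciparum* is present. These are different questions. They give different answers for mixed infections, the very patients the word mono-infection is there to exclude.

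If such a patient is kept, two things are at stake. The first is the composition of the primary population, since the patient does not meet the criteria that define it. The second is the early-failure classification in Appendix 3, which compares Day 2 and Day 3 parasite counts with Day 0. Section 6.1 computes density as asexual parasites per leukocyte count on the thick smear and leaves species to the thin smear. The follow-up schedule has a thin smear only on Day 0 and at clinical failure after Day 3. In a mixed infection, the counts behind the early-failure criteria could not be attributed to *P. falciparum* alone.

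**Working it through.** The point concerns wording, and the plan has no figure to reproduce. The check sets the texts side by side and follows one patient through them.

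**1. The criterion in each place**

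| Place | Requirement | Consequence if not met |
| --- | --- | --- |
| Summary 1.0, criterion 6 | mono-infection | not eligible |
| Section 5.2, Day 1 criterion 1 | mono-infection | excluded on Day 1 |
| Section 7.1 | mono-infection | excluded on Day 1 |
| Appendix 1, Day 1 box | mono-infection | excluded on Day 1 |
| Appendix 8, item 12 | *P. falciparum* infection | excluded only on a shaded answer |

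Item 13 of the form carries the same density limits as Section 5.2. Of the two Day 1 criteria, only the species item differs from the protocol text.

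**2. A patient with *P. falciparum* and a second species on the Day 0 thin smear**

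- Under Sections 5.2 and 7.1 and Appendix 1, the patient fails the criterion and is excluded on Day 1.
- Under item 12 read literally, *P. falciparum* is present and the answer is YES. Item 12 belongs to an inclusion block, where YES is the passing answer, so the form does not trigger exclusion.

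The shading is not visible in the text available for review. The reasoning needs only that YES passes an inclusion item. The column order supports this: it is YES then NO for inclusion items and NO then YES for exclusion items, so the passing answer always comes first.

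**3. Would another step catch the patient?**

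- The Day 1 list in Appendix 2 covers evaluation, temperature and fever history, dosing, and a smear if there are danger signs. It has no species check.
- Item 45 of the clinical record form records species but has no exclusion instruction.
- The reasons for exclusion after enrolment, in the protocol text and on the record form, are outside antimalarial use, concomitant febrile illness and withdrawal of consent. The record form also allows for loss to follow-up and for an error that prevented classification. None of these names a mixed infection noticed after Day 1.

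Item 12 is therefore the only form field that ties species to exclusion.

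**4. Can the effect be sized?**

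Let a fraction m of an arm be retained mixed infections with failure risk q, and let p be the failure risk in the other patients. The arm's expected failure proportion is (1 − m)p + mq, which differs from p by m(q − p). For the same m in both arms, the treatment difference shifts by m[(q₁ − p₁) − (q₀ − p₀)].

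Section 8.1 gives planning values for p (15% against 5%, or 10% against 2%). The documents give neither m nor q. If mixed infections fail at the same rate as other patients in each arm (q = p), the shift is zero. No number can be put on it from the documents.

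**The case against.** The strongest reply is that the protocol text is clear and consistent in four places, and a form cannot override it. Items 12 and 13 match the two Day 1 criteria of Section 5.2 one for one, so item 12 can be read as shorthand for the first. There are other controls too. Experienced technicians outside direct patient care read the thin smear for species (6.1), staff are trained in the protocol and tested (9.2), and the co-ordinator transfers laboratory results and reviews the record forms (9.1, 9.2). Species is recorded at item 45, so the criterion can be recovered.

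Much of this stands. A reader might infer that mixed infections are in fact kept, dosed and followed to Day 28. The documents do not support that, because Sections 5.2 and 7.1 and Appendix 1 all direct exclusion on Day 1. Nor does the form reverse the rule: it drops a qualifier and nowhere tells staff to keep a mixed infection.

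A reader might also infer that removing such patients late would bias the comparison. That does not follow. Species is a pre-treatment characteristic, and Section 4.4 keeps laboratory staff blinded to treatment group. Removal on the Day 0 species reading does not by itself select on outcome. Randomisation should also balance any retained mixed infections between arms on average.

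What the reply does not remove is the mismatch. The form is completed for the Day 1 decision and has its own exclusion instruction, so its wording ought to carry the criterion and not depend on staff to supply the missing word.

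**Conclusion.** The point holds as a minor error: item 12 is wrong as written. Read literally, the Day 1 eligibility form passes a mixed infection that the protocol excludes, so staff who rely on it can retain patients outside the primary population. This rests on two assumptions: YES passes an inclusion item, and some staff may work from the form without checking the protocol text.

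The size is unknown because the documents give no mixed-infection rate. No bias in the treatment comparison, and no direction of bias, has been shown. The sample size and the definition of the primary population are unaffected.

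**What to change.** Reword item 12 of the screening form so that it asks for *P. falciparum* mono-infection, as in the Summary, Sections 5.2 and 7.1 and Appendix 1, and check that NO falls in the shaded column.

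For any patients already enrolled on the present form, list the Day 0 species entry (item 45 of the clinical record form) and apply the mono-infection criterion from it. Do this blind to treatment and outcome, before the primary population is fixed, and report the number affected in each arm.

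The cost is one line on one form and one data listing. The thin smear and the species entry are already collected, and no new eligibility rule is introduced.
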